### Relevant concomitant care permitted or prohibited during the trial {11d}

There is no restriction on concomitant care during the trial.

### Provisions for post-trial care {30}

Post-trial care will follow routine NHS practice in each centre. In centres where ultrasound imaging is used as the 4–12-week follow-up and/or at 1 year, these patients will be required to undergo one additional CT angiography. This deviation from standard care has been noted in the application for ethical approval for the study.

### Outcomes {12}

#### Primary outcome

Primary efficacy parameter of the study is procedure duration, measured as the time between insertion of the first wire (after percutaneous access achieved, if applicable) at the beginning of the endovascular procedure to the last frame of the completion angiogram. This will be recorded (in minutes) at the time of the procedure by the local research team.

#### Secondary outcomes

Procedural efficiency:Anaesthetic duration—the time between the beginning of induction and the end of emergence. This will be documented at the time of the procedure by the local research team in minutes.X-ray dose per procedure—fluoroscopy time (FT) (seconds), dose area product (DAP) (Gy.cm2) and cumulative air kerma (CAK) (mGy) should be recorded and documented at the time of the procedure by the local research team. The imaging system used should also be recorded.Contrast dose per procedure—the volume (ml) and concentration (mgI/ml) of the iodinated contrast material used should be recorded by the local research team at the time of the procedure in minutes.Consumable use in the operating theatre for endovascular aortic aneurysm repair—name of device, unit and quantity used, blood products used; details to be completed by nurse in the operating theatre or research nurse at the time of the procedure.Technical success:Proximal and distal seal zone at least 10mm and no evidence of endoleak. This will be documented by the imaging CoreLab team on review of the CT images acquired post-operatively and at 4–12 weeks and at 52 weeks.Patient outcomes:Length of ICU/HDU admission—date and time from admission to date and time of discharge from ICU/HDU; documented by the local research team during the time of admission; ICU and HDU admissions should be documented separatelyPostoperative length of hospital stay—date of procedure to date of discharge from hospital (nights); documented by the local research team during the time of admission.30-day mortality—death of the participant within 30 days of the primary procedure; documented by the local research team; to include date of death (dd/mm/yy) and cause.Re-intervention—any procedure open surgical or endovascular undertaken within 1 year of the primary endovascular aortic aneurysm repair procedure (binary outcome). The type, timing, and number of procedures should also be recorded by the local research team.Adverse events—hospitalisation for any reason within one year of the primary endovascular aortic aneurysm repair; the type of event should be documented and classified as one of the following: musculoskeletal, urological, neurological, ophthalmological, cardiovascular, gastro-intestinal, hepato-pancreato-biliary, dermatological, or other by the local research team, with information captured to understand if linked to re-intervention. For each hospitalisation, the following should also be captured:i.Day case, elective, non-electiveii.Length of hospital stay—date of admission to date of discharge (nights)iii.Length of ICU/HDU admission (if applicable)—date and time from admission to date and time of discharge from ICU/HDUQuality of life—differences in quality of life between intervention and the comparator group and changes in quality of life post-surgery will be measured using data from the patient-completed EQ5D-3L [11] instrument. EQ-5D-3L is a validated measure of health-related quality of life, consisting of a five-dimension health status classification system and a separate visual analogue scale. EQ-5D-3L data will be obtained through face-to-face or telephone interview with the participant at baseline, pre-discharge, 4–12 weeks, and at 12 months follow-up.Cost-effectiveness, as assessed by:Total resource use and costsQuality-adjusted life years (QALYs)—quality of life will be measured by the EQ-5D-3L instrument as described above. In order to be used in the calculation of quality-adjusted life years (QALYs), the EQ-5D-3L dimension scores will be converted to utilities using the relevant value set for England. Quality-adjusted life years (QALYs) gained in both groups, over the time horizon of the trial, will be calculated using the area under the curve method.Incremental cost per QALY

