#### Intervention delivery

Procedures will be performed under local, regional or general anaesthesia (likely ratio: 1:1:8). Procedures can be undertaken using either a mobile C-arm in a surgical operating theatre, a dedicated fixed fluoroscopy set, or in a hybrid operating room. Patients may go to the ward, HDU, or ICU following the procedure, according to local protocol. Routine pre-operative CT aortic imaging will be used to determine general suitability for endovascular repair, including assessment of landing zones for fixation and sealing, and procedure type and device selection.

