### Recruitment {15}

Evidence-based site selection was used to confirm the eligibility of each centre to participate in the trial using volumes of endovascular repair of infra-renal and thoraco-abdominal aortic aneurysms listed on the National Vascular Registry as well as a record of satisfactory patient outcomes and strong clinical engagement. During the trial, the team will maintain regular contact with the sites, undertake regular site visits, and ensure there are adequate numbers of randomisers at sites and that Cydar EV is installed in as many rooms as required. These will be supplemented by in person local principal investigator and research nurse meetings where site teams can hear the experience of other sites and problems and tips and tricks to ensure strong participant recruitment can be shared.

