## Assignment of interventions: allocation

### Sequence generation {16a}

Once baseline assessments are complete, participants will be randomised in a 1:1 ratio using the method of minimisation. Randomisation is at the patient level and is performed using a web-based bespoke randomisation system set up by the King’s Clinical Trials Unit (KCTU) at King’s College London. Randomisation is minimised by the following factors:SurgeonProcedure urgency: emergency or electiveProcedure type: simple (repair of infra-renal aneurysm ± internal iliac embolisation) or complex (all other types of AAA and TAAA repair, to include branched and fenestrated devices)

The procedure is as follows: on receipt of the baseline questionnaire, the trial coordinator electronically submits details of each participant to the CTU. This includes participant ID number, site, initials, and date of birth. The system immediately notifies the relevant study nurse and records the randomisation outcome. The trial coordinator does not receive the randomisation outcome.

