### Implementation {16c}

Patients will be enrolled in the ARIA trial by the local trial team at each of the participating sites as per the described consenting procedure. The allocation sequence generation will be implemented via the Kings College Trial Unit (KCTU) web-based randomisation system. The randomisation of participants will be performed post-consent, after checking their eligibility. The signed consent form will be made available for the operating team to review, along with the randomisation result. Participants will be randomised to Cydar-EV image fusion for guidance or standard imaging techniques in a ratio of 1:1 post-consent and confirmation of eligibility.

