#### Statistical methods for primary outcome

As the primary outcome is procedure duration and we envisage 7.5% loss of patients between randomisation and procedure, the primary analysis will be a per-protocol (PP) analysis based on procedure time. The primary analysis will be conducted after completion of first follow-up (at 4–12 weeks) which will include procedure time as well as the secondary outcome data available at this time. Sensitivity analysis with multiple imputation for missing data will also be conducted alongside the per-protocol analysis. No significance tests will be performed for baseline comparison. The primary outcome measure is likely to have a skewed distribution and therefore if necessary and possible the data will be normalised using an appropriate transformation. The data will then be analysed using linear regression techniques with stratification (minimisation) factors included as covariates. If a suitable transformation cannot be found, the data will be analysed using quantile regression to allow us to include the addition of the stratification factors as covariates.

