#### Statistical methods for secondary outcomes

A similar analysis will be undertaken for the secondary outcomes including quality of life scores. Binary outcomes will be compared between arms using logistic regression adjusting for stratification factors. Outcomes will be reported as adjusted differences in means (or median) or odds ratios for continuous and binary data respectively. All tests will be two sided and will be assessed at the 5% significance level. Safety outcomes will be reported as patient proportions and rates within and between arms with 95% confidence intervals using exact methods where appropriate.

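### Nothing requires the imaging system to be fixed before randomisation, and it is not among the stated covariates, so the DAP and air-kerma comparison loses precision and is left open to an allocation-related difference in systems

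*Protocol article*

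**What the plan says.** All references are to the protocol article.

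- **Systems allowed** (Intervention delivery): "Procedures can be undertaken using either a mobile C-arm in a surgical operating theatre, a dedicated fixed fluoroscopy set, or in a hybrid operating room". No rule is given for choosing among them, and no time by which the choice must be made.
- **Outcome** (Secondary outcomes, X-ray dose): besides fluoroscopy time, "dose area product (DAP) (Gy.cm2) and cumulative air kerma (CAK) (mGy) should be recorded". The same item adds "The imaging system used should also be recorded". No use of that record is stated.
- **Balancing** (Sequence generation {16a}): "Randomisation is minimised by the following factors". The list is surgeon, urgency, and simple or complex procedure. Imaging system and room are not on it.
- **Model**: the primary outcome is analysed by "linear regression techniques with stratification (minimisation) factors included as covariates". For the rest, "A similar analysis will be undertaken for the secondary outcomes including quality of life scores". The stated covariates for dose are therefore the same three factors.
- **Knowledge of allocation**: the trial is open label and Table 1 lists treating clinicians as unblinded. Under Implementation {16c}, "The signed consent form will be made available for the operating team to review, along with the randomisation result".
- **Availability of the device** (Recruitment {15}): the team will ensure that "Cydar EV is installed in as many rooms as required".

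**The concern.** DAP and air kerma plausibly depend on the X-ray equipment as well as on how the operation goes. The instruction to record the system alongside dose suggests that the authors think so too, although they give no reason for it. If the arms differ in the mix of systems, part of any dose difference belongs to the room and not to Cydar EV.

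A route for this exists. An intervention patient needs a room with Cydar EV and a control patient does not. The operating team has the allocation, and the sample size section expects 7.5% of patients to be lost between randomisation and procedure, so there is an interval in which bookings could be made or changed. Minimising on surgeon broadly balances hospital, but not the room that a given surgeon uses.

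The Background names lower X-ray exposure as an expected benefit, so the dose result will be read closely. Even if the room has nothing to do with allocation, leaving a strong determinant of dose out of the model widens its confidence interval.

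**Working it through.** **The plan's own figure.** The article states no figure for X-ray dose. Its only calculation is for procedure time. Control CV = 69.2/132.1 = 0.524, so log-SD = √ln(1 + 0.524²) = 0.492. Then n = 2(1.960 + 1.282)² × 0.492² / (ln 1.2)² gives 154 per arm (155 with the noncentral t), against 153 stated. Allowing for 10% loss, 153/0.90 = 170. This reproduces, and it has no bearing on dose. It is used below only for n = 153 per arm.

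**Assumed inputs, none of them in the article.** The dose ratio between two system types is r = 1.5 to 3. The difference between arms in the share of cases on the higher-dose system is d. The residual SD of log dose is s = 0.7. Systems are split 50:50 and are independent of surgeon, urgency and procedure type.

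**Shift in the dose ratio if the mix differs.** Apparent ratio with no true effect = exp(d × ln r).

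| r | d = 0.10 | d = 0.20 |
|---|---|---|
| 1.5 | 1.041 (4%) | 1.084 (8%) |
| 2 | 1.072 (7%) | 1.149 (15%) |
| 3 | 1.116 (12%) | 1.246 (25%) |

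The direction depends on which arm has more cases on the higher-dose system, so the shift could favour either arm. At r = 2 and s = 0.7 with 153 per arm, a systematic 10-point imbalance raises the false-positive rate of the dose test from 5% to about 12%, and a 20-point imbalance raises it to about 34%.

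**Chance imbalance.** If room choice is unrelated to allocation, the SD of the difference in shares is √(2 × 0.25/153) = 0.057, so 95% of trials fall within about ±11 points. This is not bias. The 5% test level and the confidence interval already allow for it.

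**Precision.** Relative reduction in standard error from adjusting = 1 − √[s² / (s² + 0.25 (ln r)²)], with s² = 0.49.

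- r = 1.5: 1 − √(0.49/0.531) = 3.9%
- r = 2: 1 − √(0.49/0.610) = 10.4%
- r = 3: 1 − √(0.49/0.792) = 21.3%

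These are upper values. Surgeon and procedure type may already track the system, in which case the gain is smaller.

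**The case against.** The strongest objection is that the bias needs room choice to depend on allocation, and the article does not say that it does. A reader might infer that the system is chosen once allocation is known, or picture a site with one equipped hybrid room to which every intervention patient must go. The text supports neither. It does not say when, by whom or on what basis the room is chosen, and it describes no such site. The commitment to equip rooms as needed points the other way. So does the Background, which says that the device runs on fixed or mobile equipment and needs no new hybrid room. This objection stands against any claim that bias is present. It does not remove the gap, because being able to run on any system is not the same as being installed on every one, and nothing fixes the room before randomisation.

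A second objection is that an extra covariate for a secondary outcome is ordinary matter for the statistical analysis plan, which is not shown. The full protocol or the case report form may also hold more than the article. That is fair as to the covariate, and it lowers the weight of the point. An analysis plan alone cannot supply a planned system recorded before randomisation, however. Without that record it can adjust only for the system actually used, which is a post-allocation variable and may itself be a result of the allocation.

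A reader might also extend the argument to procedure time, or ask that control patients be placed in equipped rooms. Neither follows. The documents offer nothing to support an effect of room on procedure time. Placing controls beside the device would also have to be weighed against the article's restriction on cross-over and the 2.5% that it allows for on-table deaths and cross-overs together.

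**Conclusion.** The point holds in a limited form. The imaging system is recorded with dose, but it is not balanced directly, is not among the stated covariates and is not required to be fixed before allocation. This leaves a route to bias in the DAP and air-kerma comparison, which the documents do not show to have been taken, and a loss of precision that applies in either case if systems differ in dose. The argument is weaker for fluoroscopy time.

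The sizes are a 4% to 12% shift in the dose ratio per 10-point imbalance, and a standard error up to 4% to 21% smaller with adjustment. Both rest wholly on the assumed dose ratio, and the second also on the assumed residual SD, the even split and independence from the existing covariates. This is a worthwhile, low-cost improvement to one secondary outcome and no threat to the primary result.

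**What to change.** 1. Enter the planned imaging system type (mobile C-arm, fixed set, hybrid room) as a baseline field before randomisation.
2. Add planned system type as a covariate in the DAP and cumulative air kerma models, beside the minimisation factors.
3. Tabulate the system actually used by arm. Adjust for it only in a sensitivity analysis, described as conditioning on a post-allocation variable.
4. For patients already randomised, take the planned system from a booking documented before randomisation where one exists. Otherwise they enter only the sensitivity analysis.

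The cost is one extra field and one covariate. The limitation is incomplete capture: recruitment began in May 2022 and was expected to end in December 2023, while the current protocol version is dated May 2023, so a new field would miss those already enrolled. The sample size and the procedure-time model do not change.

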#### Secondary objectives

The secondary objectives of this study are to evaluate the following:Procedural efficiency, as assessed by:aAnaesthetic durationbX-ray dose per procedurecContrast dose per proceduredConsumable use per procedureTechnical effectiveness, as assessed by proximal and distal seal zones at least 10 mm and no evidence of endoleakPatient outcomes, as assessed by:aLength of ICU admissionbLength of HDU admissioncPost-operative length of hospital stayd30-day mortalityeRe-intervention—primary hospital visit/further admission (HRG/procedure code)fAdverse events (category, LoS, HDU, ICU, general ward)gQuality of life (EQ5D)Cost-effectiveness, as assessed by:aTotal resource use and costsbQuality-adjusted life years (QALYs)cIncremental cost per QALY

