### Sample size {14}

There is no known minimum clinically important difference (MCID), and part of the aim of the study is to better characterise the clinical benefit to patients. The study is therefore powered on the basis of a minimum economically meaningful difference. Previous work at Duke [9] reported data on the primary outcome, procedure time, and found a mean difference of 22.5 min (17%) for patients with an abdominal aortic aneurysm treated with Cydar-EV 109.6 (34.2) and standard 2D fluoroscopy imaging 132.1 (69.2) minutes. This is a meaningful difference in the NHS context as this time reduction per case would allow four rather than three EVAR procedures to be performed per day, which is a productivity increase of 33% at the same capacity. The SD for procedure time increases with the mean and so we have assumed a *t*-test for ratio of means 1.2 (fold change), assuming a lognormal distribution for the calculations. Therefore, a sample size of 153 patients per arm with a 1:1 allocation ratio (2 × 153 = 306) would give us 90% power at the 2-sided 5% significance level to detect this difference (PASS 15 Power Analysis and Sample Size Software (2017)). Since our primary outcome measure requires the procedure to be completed, we need to inflate the sample size for possible: (i) loss post randomisation, pre-procedure (est. 7.5%), and (ii) on-table death and cross-overs (where surgeons may use the intervention in a control arm patient and additional assistance is required to complete the operation) (est. 2.5%). These inflate the sample size to 170 per arm. The final randomisation target is therefore 2 × 170 = 340. The Duke data also showed using Cydar-EV in TAAA showed larger reductions in operating time than for AAA. We have powered on the more conservative difference since the relative proportions of AAA/TAAA patients anticipated in our proposed trial is unknown.

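### Re-intervention is defined as any open or endovascular procedure within a year, so operations unrelated to the repair count and would pull the odds ratio towards 1

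*Protocol article*

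**What the plan says.** The Secondary outcomes section of the Protocol article counts as a re-intervention "any procedure open surgical or endovascular undertaken within 1 year of the primary endovascular aortic aneurysm repair procedure (binary outcome". The index repair appears in this rule only as the start of the one-year clock.

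Three other statements bear on the meaning:

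- The same item adds: "The type, timing, and number of procedures should also be recorded by the local research team". These details are collected but do not restrict the binary outcome.
- The adverse-event item that follows covers hospitalisation for any cause, classified by body system, "with information captured to understand if linked to re-intervention".
- Secondary objectives lists re-intervention with the gloss "primary hospital visit/further admission (HRG/procedure code", which also has no anatomical or causal limit.

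On analysis, Statistical methods for secondary outcomes says: "Binary outcomes will be compared between arms using logistic regression adjusting for stratification factors". It also says: "All tests will be two sided and will be assessed at the 5% significance level". Results for binary outcomes are to be reported as odds ratios.

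**The concern.** Background and rationale {6a} explains why this outcome is of interest: errors in device positioning can lead to secondary interventions, and the image-fusion system is expected to make positioning more precise. Only procedures that follow from the repair can respond to that mechanism. A hernia repair or a coronary stent cannot, yet the written rule scores each as a re-intervention.

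Two consequences follow. The reported rate in each arm would be higher than what a reader understands by re-intervention after aneurysm repair. A background of events common to both arms would also dilute the comparison, so that a real reduction in repair-related procedures is harder to see. The rule is stated explicitly, so an analysis plan that follows the protocol inherits it.

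**Working it through.** **The plan's own figure.** No event rate, effect size or power is given for re-intervention. The statement that the sample "would give us 90% power at the 2-sided 5% significance level to detect this difference" concerns procedure time only. That figure reproduces. The coefficient of variation is not stated, so the control-arm value is used:

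- CV = 69.2/132.1 = 0.524, so the log-scale SD = √ln(1 + 0.524²) = 0.492.
- With a ratio of 1.2, 90% power and two-sided 5%, n = 154 per arm by the normal approximation, against 153 stated.
- 153/0.90 = 170 per arm, as stated.

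The present point leaves this calculation untouched.

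**Inputs for the illustration.**

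- From the document: 170 per arm (Sample size {14}), two-sided 5%, odds ratio as the reported measure.
- Assumed: related-event risks p₀ (standard) and p₁ (Cydar EV), and a risk u of an unrelated procedure that is equal in both arms and independent of related events.

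**Formulas.**

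- Counted risk in arm i: qᵢ = 1 − (1 − pᵢ)(1 − u).
- Risk difference: q₀ − q₁ = (1 − u)(p₀ − p₁).
- Odds ratio: [q₁/(1 − q₁)] / [q₀/(1 − q₀)].
- Power: two-proportion normal approximation.

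**One case in full: 10% v 5%, u = 10%.**

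- q₀ = 1 − 0.90 × 0.90 = 0.190 and q₁ = 1 − 0.95 × 0.90 = 0.145.
- Odds ratio without unrelated events: (0.05/0.95)/(0.10/0.90) = 0.47.
- Odds ratio with them: (0.145/0.855)/(0.190/0.810) = 0.72.
- Risk difference: 5.0 points becomes 4.5 points.
- Standard error of the risk difference at 170 per arm: √[(0.10×0.90 + 0.05×0.95)/170] = 0.028 becomes √[(0.190×0.810 + 0.145×0.855)/170] = 0.040.
- Power: 42% becomes 20% (38% becomes 18% at 153 per arm).

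The risk difference therefore shrinks slightly and is estimated less precisely. On the log-odds scale the standard error falls, because there are more events, but the log odds ratio falls by more. The loss of power is the same in substance.

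**Range of assumptions, 170 per arm.**

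| Related risks (assumed) | u (assumed) | Counted risks | Odds ratio | Power |
|---|---|---|---|---|
| 10% v 5% | 0 | 10.0% v 5.0% | 0.47 | 42% |
| 10% v 5% | 5% | 14.5% v 9.75% | 0.64 | 27% |
| 10% v 5% | 10% | 19.0% v 14.5% | 0.72 | 20% |
| 10% v 5% | 20% | 28.0% v 24.0% | 0.81 | 13% |
| 15% v 7.5% | 0 | 15.0% v 7.5% | 0.46 | 59% |
| 15% v 7.5% | 10% | 23.5% v 16.75% | 0.66 | 34% |
| 20% v 10% | 0 | 20.0% v 10.0% | 0.44 | 74% |
| 20% v 10% | 10% | 28.0% v 19.0% | 0.60 | 50% |

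The direction is the same in every row. The amount depends entirely on rates that the document does not supply.

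**The case against.** The best defence is that the context narrows the meaning. The word re-intervention suggests a return to the same problem. Asking whether a hospitalisation is linked to re-intervention makes little sense if every operation already qualifies. The recorded type, timing and number would allow a narrower outcome to be derived, and the full protocol or analysis plan may do so. This is a fair account of the likely intent. It does not change the rule, which says any procedure and states no limit. With recording by local teams at 10 centres and unblinded outcome assessors (Table 1), an unwritten restriction could also be applied unevenly.

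It can also be said that counting every procedure avoids subjective judgements of relatedness in an open-label trial, that equal dilution does not inflate the type I error, and that no power was claimed for this outcome. All three are true. The first is an argument for a fixed list applied without arm labels and for keeping the all-procedure count alongside. The others limit the weight of the point without removing it.

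A reader might infer more than the document supports:

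- **Planned stages scored as failures.** The minimisation factors include repairs that are "complex (all other types of AAA and TAAA repair, to include branched and fenestrated devices", but the article never mentions staged repair and does not call a re-intervention a failure. Technical success is a separate, CT-based outcome. All that can be said is that the wording does not exclude planned procedures.
- **A biased cost-effectiveness result.** The economic outcomes rest on total resource use, costs and QALYs. No section feeds the binary re-intervention rate into a model.
- **Two rival definitions.** The gloss in Secondary objectives can be read as the setting of the re-intervention and how it is coded. It is loosely worded and need not conflict with the definition.

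**Conclusion.** The point holds for one secondary outcome. The written definition admits procedures with no connection to the repair. It therefore overstates the re-intervention rate and, if such procedures occur equally and independently in both arms, draws the odds ratio towards 1 and reduces power. How much cannot be determined from the document. Under assumed related risks of 10% v 5%, unrelated rates of 5% to 20% give odds ratios of 0.64 to 0.81 in place of 0.47. Even a perfectly specific definition would have modest power at the lower assumed rates (42% in that case), so the main gain is an interpretable estimate. The primary outcome, its analysis and the sample size stand.

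**What to change.** Before outcome data are inspected, define re-intervention as an open or endovascular procedure, within 1 year of the index repair, that is either on the aorta, the implanted device, a treated branch or an access vessel, or performed for a complication of the index repair. The last clause keeps operations elsewhere in the body that result from the repair.

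Derive the outcome from the recorded procedure type using a prespecified list, applied without arm labels. State whether planned procedures count. Report the number of patients with any procedure as a supportive outcome, and retain all procedures for resource use. Bring the wording in Secondary objectives into line.

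The cost is a change of wording, a small classification task and fewer counted events. Type, timing and number are already collected. Where a procedure type does not show whether it treated a complication, or whether it was planned, this may need checking against source records.
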